**Figure 1 Fig1:**
[figure not shown]
**TOPMED final trial design (see accompanying file).**

These components consist of three aspects aimed at the clinic level: 1) incentives with audit and feedback based on overall and incremental goal performance; 2) an HIT system called the Integrated Care Coordination Information System (ICCIS) that measured care on individual patients as well as progress towards clinic goals; and 3) tailored practice facilitation. The sole difference between the intervention and control arm is that the control arm is given free rein to address any health reform goal and the intervention arm is encouraged—both through practice facilitation and incentives—to focus their transformation efforts on achieving as many high-value elements as possible. A summary is shown in Table 2 below. Across five topic areas for high-value elements, 12 subtopics were developed into 26 specific measures that allow flexibility and increase achievement. Components such as identification of at-risk population and care management are measured by provision of care plans, offering advanced directives, and outreach to high-risk populations. Patient engagement and proactive goal setting involve self-management support and reminders. Integrating information focuses on clinical information exchange and follow-up post-utilization, while population management focuses on the use of population management tools to proactively manage metrics and certain outreach components. Finally, access was added based on patient-identified need; after-hours access and availability of providers are the identified elements from the focus group. Alignment with health reform metrics is moderate to strong. Moderate alignment was defined as some overlap with the general area of health reform, but the metric did not exist in the reform model. For instance, risk stratified care management concepts were not measures in the reviewed initiatives but rather general goals. Strong alignment means that the precise measure was or is in place elsewhere, but the benchmark was more advanced or specific. For instance, follow-up on utilization is a specific CPC metric, but the study benchmark of 70% is more aggressive.

**Table 2 Tab2:** **Intervention ‘high-value’ elements**

**Element**	**Description**	**Specific example metric** ^*****^	**Alignment with reform**
Identification of at-risk populations and care management	Care plan utilization	Tier 3—PCMH provides care plans to >50% of high-risk patients.	Moderate
	Advance directive utilization	Tier 3—The PCMH offers advance directives to at least 50% of patients over 65.	
Based on need	Care management outreach	Tier 2—PCMH’s care coordination outreach reaches 50% of high-risk patients.	
Patient engagement and proactive goal setting	Education and self-management resources	Tier 2—More than 10% of all unique patients are provided patient-specific education resources and self-management services.	Strong
	Reminders	Tier 3—PCMH sends appropriate reminders to at least 20% of all eligible patients.	
Integrated information and procedures across settings	Clinical information exchange	Tier 1—PCMH exchanges structured clinical information and tracks critical elements (e.g., hospitalizations).	Strong
	Utilization monitoring and follow-up	Tier 3—PCMH follows up on patient hospitalizations and ED visits 70% of the time (when they have the information).	
Population management tools	Performance data utilization	Tier 1—The PCMH uses performance data to identify opportunities for improvement and acts to improve clinical quality, efficiency, and patient experience.	Strong
	Receive and respond to electronic requests	Tier 3—The PCMH provides a response to online or electronic queries within two business days.	
Improved access	After-hours access	Tier 1—PCMH offers access to in-person care at least 12 h weekly outside traditional business hours.	Strong
	Tracking 3rd next available appointments		

*Nine metrics are solely applicable to primary care, and eight include primary care and other aspects of the health care system.

### Trial implementation and monitoring

Clinics are eligible for the same amount of incentives. Practice facilitation is offered monthly to both intervention and control since recent summary literature suggests that practice facilitation both makes it possible to transform and directly affects outcomes of trials. At each visit, clinics are free to select from a wide variety of choices based on their current needs; while the control arm has 35, the intervention arm has 12 options. Previous goals are assessed by the practice facilitator and new ones set. The IT system is available at all times, with functions of risk stratification (built in scores), care management tracking, and self-assessment of all PCMH elements available for clinical team review. The incentive reports are built into the IT system, with the intervention and control receiving a general score based on setting and meeting QI goals, and intervention receiving a multiplier based on the number of high-value elements met. The multiplier, whose maximum was 2, set 30% of the potential incentive aside for HVE achievement. Once the clinics meet a HVE threshold of 2/3 of the elements achieved, they earn up to a 10% bonus for achieving additional elements. Additional file 1 shows the proposed IT reports for intervention and control.

The process to generate the scores was tested during the pilot study. In general, effort at QI is rewarded on a 0%–100% scale; factors included in the score generation are organization around QI, leadership involvement, team function, and setting and follow-up on goals. From the practice facilitator’s notes each month, a team of three investigators review each element and decide on a total score. This score is fed back at each visit, with a summary report of overall performance versus other clinics each quarter. The pilot clinic demonstrated a strong response to the reward of effort and the competition engendered by a ‘grading’ approach; they did require significant explanation of the scoring rubric and requested the opportunity to offer feedback to get a score adjusted.

### Outcomes and measures

There are three sets of measures planned for the trial. First, primary and secondary outcomes are aligned with the triple aim for cost/utilization, experience of care, and population health, with specific expected decreases planned as clinically meaningful and to set sample size. Primary outcomes are reduction in total cost of care for patients, with a focus on hospitalization rate and ED visit rate of patients as indicator measures. A reduction in utilization up to 20% per year has been seen in some related studies, but a conservative estimate of 10% relative reduction in utilization is planned for this study. Measurement of this outcome will be completed through a state-based All Payer All Claims database, which allows for attribution of patients to a clinic based on visits to primary care, and contains all claims for that individual across insurance types. This outcome and its specific measurement are strongly related to the health reform goals, using the same metrics for success. For experience of care, the Clinician and Group Consumer Assessment of Healthcare Providers and Systems (CG-CAHPS) surveys at the patient level will be used, with an expectation of a 10% improvement in experience of care metrics closely related to the high-value elements. There are 11 composite scores, and 4 are determined to be closely aligned to the study aims: 1) providers support you in taking care of your own health; 2) providers pay attention to your mental or emotional health; 3) follow-up on results; and 4) access to care. A secondary outcome is a composite quality score at the clinic level based on standard chronic illness health reform measures used for the clinics. A 10% increase is expected in the *control* clinics, since previous work has shown that clinics often focus on common quality measures first. Table 3 outlines primary, secondary, and monitoring outcomes, along with their respective metrics and data sources.

**Table 3 Tab3:** **Primary, secondary, and monitoring outcomes**

	**Metrics**	**Measurement source**	**Alignment with health reform**
*Primary outcome goals*			
Reduce utilization by 10%	*Total cost of care*	All Payer All Claims data source; *patient level*	Strong; primary goal
	Hospitalization rate per patient per month		
	ED visit rate per patient per month		
Improve experience of care by 10%	CG-CAHPS: 4/11 composite scores	Survey to 1,600 random stratified *patients*	Strong
*Secondary outcome goals*			
Improve quality of care by 10%	Composite of nine composite measures	EHR-based electronic clinical quality measures; *clinic level*	Strong: same measures used
Improve teamness, collaboration, and patient-centered care	Composites of various tools	CSQ, TDM, CPAT, and novel collaboration tool; *clinic level*	Indirect
*Monitoring goals*			
Clusters engage in quality improvement	Monthly ‘score’ based on QI progress and goal setting	Novel practice facilitation-based measure; *clinic level*	Moderate
HVE passed monthly	Monthly count of HVEs passed	HVEs derived from PCMH; *clinic level*	Strong

Other secondary outcomes include measurements at the cluster and patient level based on stakeholder suggestion. For clinics, culture, microsystem team performance, coordination and collaboration, and adaptive reserve were felt by stakeholders and seen in the literature to be crucial to measure before and after the trial; thus, we will use the clinician staff questionnaire (CSQ), the Team Development Measure (TDM), the Collaborative Practice Assessment Tool (CPAT), and a novel collaboration tool for external collaboration between clinical teams. Qualitative interviews with patients and with clinics will be performed to understand the impact of study more broadly. Monitoring goals were discussed above but required monthly assessments of clinic engagement with QI goal setting and follow-up as well as the high-value elements will provide protocol monitoring metrics. Deviations from protocol will be recorded and used to calculate protocol adherence.

### Sample size

The sample size was based on eight hypothetical clinics with an average of 10,000 patients each. The intracluster correlation was estimated at .02, and the necessary sample size to detect a change of 10% in cost and utilization over the year was <6,000 patients with average costs of $730 per month (average Medicare spend for our region) and average hospitalization rates of 14% at a power of > .80. Besides the monitoring metrics, above, no interim analyses or stopping guidelines were planned due to the low risk of the study.

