## Discussion

The TOPMED trial is a cluster randomized controlled trial to test whether focused quality improvement would be superior to general quality improvement in achieving cost and experience of care outcomes, especially for high-risk patients, across eight clinics. The trial has a pragmatic design, focusing on providing incentives, IT support, and practice facilitation that are intended to work in the real world of health reform and still allow choice, autonomy, and flexibility for the clinical teams.

Several trial design aspects proved challenging and have limitations. Sample size for number of clusters is low, while the patient-to-cluster ratio is high. A report by Mathematica on patient-centered medical home studies completed a quantitative analysis that concluded 200 clinics (cluster level) with 10 patients each would have significantly more power than 10 clinics with 200 patients each [13]. However, stakeholders reflected to our study team that the ability to understand what is happening in each cluster can be extraordinarily complex—a clinic is an organization made up of many different microsystems, changing processes, and subpopulations of patients who may self-select a particular microsystem based on their needs; failing to measure these microsystems leads to errors. In addition, significant resources are required to try to alter processes within a single clinic, making studies with large number of clusters expensive. Finally, measurement of processes, structure, and other aspects of performance (e.g., culture) at the cluster level (in addition to the patient level) is also resource consuming and yet may be the single most important aspect of cluster RCTs—understanding processes and culture seems to dictate success in many implementation science reviews. Blinding for a trial design like this is not wholly possible. However, partial blinding was used and independent review of facilitator performance and scoring is intended to reduce this bias. For analysis, multiple publications have discussed the frequent need for *post hoc* adjustments in analyses, including intracluster correlations, two-stage analysis, instrumental variables, and propensity scoring as ways to adjust for baseline differences in the individual patients. Although we use two-stage analysis, differences in clusters or panels may still persist and affect outcomes.

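### The stated power above .80 with fewer than 6,000 patients cannot be reproduced for hospitalization from the protocol's own inputs (eight clinics, ICC .02, 14% rate, 10% relative reduction)

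*Protocol article*

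**What the plan says.** The Sample size section gives nearly all the inputs in two sentences. The design: "The sample size was based on eight hypothetical clinics with an average of 10,000 patients each". The clustering: "The intracluster correlation was estimated at .02". The claim: "the necessary sample size to detect a change of 10% in cost and utilization over the year was <6,000 patients". The cost input is a mean of $730 a month. For hospitalization, the input and the power claimed are: "average hospitalization rates of 14% at a power of > .80".

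The Outcomes and measures section fixes the 10% as relative: "a conservative estimate of 10% relative reduction in utilization is planned for this study". The Randomization section allocates matched pairs of clinics, so there are four clinics per arm. The Statistical methods section plans a between-arm difference-in-difference that allows for the intracluster correlation.

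The Discussion admits that there are few clusters and reports that an outside analysis "concluded 200 clinics (cluster level) with 10 patients each would have significantly more power than 10 clinics with 200 patients each". It does not return to the power figure. Alpha, the standard deviation of cost and any baseline-to-follow-up correlation are not stated.

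**The concern.** With few clusters and many patients per cluster, between-clinic variation dominates the standard error, and further patients add almost nothing. At ICC .02, eight clinics are worth at most 8/.02 = 400 independent patients in a follow-up comparison. A fall of 1.4 percentage points from 14% is small against that, so power above .80 looks wrong on sight. The unclustered requirement also looks larger than 6,000.

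Cost, hospitalization and emergency visits make up the first primary outcome goal. If the stated power stands, a null result will be read as coming from a trial able to detect a 10% change, and so as evidence that focusing on high-value elements does not reduce utilization.

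**Working it through.** **Inputs.** From the protocol: 8 clinics, 4 per arm; ICC .02; hospitalization 14.0%; 10% relative reduction, so 12.6% and a difference of .014; fewer than 6,000 patients, read as a trial total of 750 per clinic; also 10,000 per clinic. Assumed: two-sided alpha .05. The 14% is read as a yearly proportion.

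**1. Trying to reproduce the stated figure, without clustering.** Variance sum V = .14×.86 + .126×.874 = .2305.
- Patients per arm for 80% power: (1.960 + .842)² × .2305 / .014² = about 9,231, or about 18,460 in total.
- 6,000 in total (3,000 per arm): SE = √(.2305/3,000) = .00877; .014/.00877 = 1.60; power 36% (48% one-sided).
- 6,000 per arm: power 62% (73% one-sided).

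Three other readings are compatible with fewer than 6,000 patients and power above .80: a one-sample test without clustering (4,696 patients); a 20% reduction without clustering (2 × 2,204 = 4,408); and a 10-point absolute fall, 14% to 4%, with clustering (82% by t, 93% by normal approximation). Each contradicts the protocol's own description: a between-arm comparison, a 10% relative change, ICC .02.

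**2. Adding the stated clustering, follow-up comparison only.** Design effect = 1 + (m − 1) × .02; SE = √(V × design effect / 4m).

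| Patients per clinic | Design effect | Effective N (total) | SE | Power, normal | Power, t (6 df) |
|---|---|---|---|---|---|
| 750 | 15.98 | 375 | .0350 | 6.8% | 6.3% |
| 10,000 | 200.98 | 398 | .0340 | 7.0% | 6.4% |

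With 3 df for matched pairs, power at 750 per clinic is 6.0%. The relative reduction detectable with 80% power at 750 per clinic is about 61% (normal) or 70% (t).

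**3. Crediting the planned difference-in-difference.** This needs two quantities that the protocol does not give: the clinic autocorrelation (CAC) and the within-patient correlation (IAC) between periods. The average variance is V/2 = .11526, so σ_b² = .02 × .11526 = .002305 and σ_w² = .98 × .11526 = .11296. Then

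Var = (2/4) × 2 × [σ_b²(1 − CAC) + σ_w²(1 − IAC)/m].

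Example, m = 750, CAC .95, IAC .3: .0001153 + .0001054 = .0002207; SE .0149; .014/.0149 = .94; power 15.6%.

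| m | CAC | IAC | Power, normal | Power, t (6 df) |
|---|---|---|---|---|
| 750 | .80 | 0 | 8.7% | 7.7% |
| 750 | .95 | .3 | 15.6% | 12.6% |
| 750 | 1 | .5 | 36.5% | 27.5% |
| 10,000 | .80 | 0 | 9.9% | 8.5% |
| 10,000 | .95 | .3 | 24.3% | 18.7% |
| 10,000 | .99 | .5 | 74.3% | 59.0% |
| 10,000 | 1 | 0 | 98.6% | 93.1% |

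Baseline adjustment instead of differencing raises the third row only to 36.9%.

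**4. Cost.** With no standard deviation the claim cannot be checked. At 750 per clinic and ICC .02, a follow-up comparison of $730 with $657 reaches 80% only if the coefficient of variation is about .35 or less (normal) or .29 or less (t).

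**The case against.** The strongest objection is that the 7% belongs to an analysis nobody plans. The protocol specifies a difference-in-difference with covariate adjustment and propensity matching, and clinics are randomized in matched pairs. This stands as far as it goes: 7% is a no-baseline reference, not the trial's power, and should not be printed as such. It does not rescue the claim, because at 750 per clinic even perfectly stable clinic effects with IAC .5 leave power at about 37%.

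A reader might also infer that power above .80 is impossible with eight clinics. The documents do not support that. At 10,000 per clinic the difference-in-difference passes 80% if the clinic autocorrelation is above .99. With autocorrelation exactly 1 and IAC .3, about 3,200 per clinic suffices by the normal approximation. That is still 8 × 3,200 = 25,600 patients, and it rests on an unstated assumption.

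Two further extensions should be resisted. Cost power cannot be called inadequate when its standard deviation is unknown. Nor should a power figure be attached to the patient-experience survey (Table 3: "Survey to 1,600 random stratified" patients), because the Sample size section claims no power for it and its ICC and baseline scores are not given.

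Finally, the Discussion does warn that clusters are few. This tempers the risk of misreading, but a general limitation does not withdraw a specific number. Nor does the condensed format of an article excuse a figure that it states.

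**Conclusion.** The concern holds for hospitalization: the stated sample size and power do not follow from the stated inputs. Power at 6,000 patients is 36% if clustering is ignored. With ICC .02 and four clinics per arm it is about 6–7% for a follow-up comparison. For the planned difference-in-difference it is about 8–16% (CAC .8–.95, IAC 0–.3), and at most about 37% in the scenarios tried. Because the sentence claims cost and utilization jointly, this failure defeats it as written.

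The conclusion rests on a two-sided 5% test and on reading 6,000 as the trial total. The one-sided and per-arm readings tried without clustering also stay below .80. The difference-in-difference figures rest on assumed correlations and are a range, not an estimate of the trial's power.

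**What to change.** In the Sample size section, withdraw both the figure of fewer than 6,000 patients and the power above .80. Restate power and the minimum detectable effect for the planned difference-in-difference with eight clinics and ICC .02. Name the assumed clinic autocorrelation, within-patient correlation, alpha and cost standard deviation, and show results over a range of each. The follow-up-only figure of about 7% may be given as a reference if it is labelled as using no baseline. Add that a non-significant result with eight clinics is not evidence of no effect.

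The trial status section says that primary data collection has ended and that analysis of the primary outcomes has not begun, so the correction is one of wording and can still precede the results. It needs no added clinics or patients. The only cost is a less favourable stated figure.

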### Randomization

For randomization, with a small number of clusters (8), the study requires significant work to assure baseline similarities, where possible, and analytic techniques to adjust for site-specific differences. To that end, we used a sequence allocation that was computer-generated and used matching by key characteristics to place the clustered clinics into match groups. Match criteria included organization type and location; total patient population, and the number of patients that were high risk according to a standardized risk scoring system based on comorbidities that predict hospitalization. Sequence generation was done by a random number seeded by time; matched pairs of clinics are randomly allocated by this seed to either intervention or control. For the patient experience of care surveys, patients are randomly chosen by a computer program, with oversampling of ‘high risk’ at 50% of the overall sample. The principal investigator (PI) wrote the randomization algorithm, the matching criteria, and had multiple team members approve them as fair, unbiased, and without error prior to implementation. Once the program was run, it was sent directly to the other team members without intervention by the PI.

### Blinding and consent

For blinding, incentives vary by arm and participants are shown their own incentives. To partially blind them, the terms ‘intervention’ and ‘control’ are not used, and all reports are only shown to individual clinics without noting differences between arms. Similarly, blinding for the study team (to avoid experimenter’s bias) is not possible, since the reports are seen across clinics by the team. To reduce bias, the practice facilitator is required to log all interactions and have these reviewed by a third party for time equality (same resource amounts provided to each), for minimal discussion of differences between clinics and arms, and for similar internal milestone achievement by each clinic. Blinding for the analyst is planned, with intervention and control arms labeled only as A and B, and clinic and patient identifiers are masked. Consent was sought from clinics, clinicians participating, and patients receiving the CG-CAHPS survey; other data collection is completed, done under a waiver of consent.

### Statistical methods and analysis

Descriptive analysis will compare baseline characteristics of clinics and individuals across outcomes and primary confounders (demographics, chronic illnesses, previous medical care, previous adherence to quality measures). A difference in difference calculation will compare changes in rates of outcomes for intervention versus control. Primary analysis will be a multi-level, two-stage analysis to account first for patient level and clinic level differences and then changes over time. Modeling will be done using generalized estimating equations; these can be adjusted for the level and the outcome variable specifics. The risk of selection bias by cluster is high, so to account for this, we pre-assess the population by risk of hospitalization using a standardized risk score prior to trial start. This group becomes the analytic cohort, and the size of each high-risk group is used to stratify clusters. We will generate the intracluster correlation, account for it by adjusting multivariate analysis, and perform propensity matching within the analytic cohort to assure similarity of baseline cohorts at the clinics. Overfitting will be tested using Copa’s test and model fit using Hosmer-Lemeshow, receiver operating curves, and Akaike information criterion for logistic-based models and Box-Cox test, GLM family test, Link and RESET test in addition to *R*^2^, and mean-squared error for cost-based models.

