### Participants

Participants are eight primary care clinics (clusters) that are deeply engaged in health reform, are willing to use a population management registry tool, are willing to receive practice facilitation and improve their performance, and use an electronic health record (EHR) system at baseline. A goal was set to recruit a diverse set of participant clinics by ownership, location (rural versus urban), and size (from 3 to 20 providers). Patients, providers, and staff of these clinics are consented separately when their specific opinions or viewpoints are elicited (via surveys or interviews), with no penalty for non-participation. Data is collected at the clinics during facilitation sessions, from the EHR through automated extraction and from patients, providers, and staff via paper and online surveys.

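### GEE is named as the modelling method for eight clinics in four matched pairs, and no stated adjustment makes its standard errors or reference distribution valid with so few clusters

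*Protocol article*

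**What the plan says.** All references are to the Protocol article, Methods/Design.

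- **Participants:** "Participants are eight primary care clinics (clusters"). Diversity in "size (from 3 to 20 providers") is given as a recruitment goal. Realised sizes are not reported.
- **Randomization:** "matched pairs of clinics are randomly allocated by this seed to either intervention or control", which makes four pairs and four clinics per arm. The same section recognises the difficulty: "with a small number of clusters (8), the study requires significant work to assure baseline similarities, where possible, and analytic techniques" to adjust for differences between sites.
- **Statistical methods and analysis:** "Primary analysis will be a multi-level, two-stage analysis to account first for patient level and clinic level differences and then changes over time". Then: "Modeling will be done using generalized estimating equations; these can be adjusted for the level and the outcome variable specifics". On clustering: "We will generate the intracluster correlation, account for it by adjusting multivariate analysis". Propensity matching within the analytic cohort and a baseline hospitalization risk score are added.
- **Sample size:** "The sample size was based on eight hypothetical clinics with an average of 10,000 patients each".

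The Discussion concedes that there are few clusters and many patients per cluster, and relies on two-stage analysis while accepting that cluster differences may persist. The article names no variance estimator, small-sample correction, reference distribution, degrees of freedom, alpha or sidedness.

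**The concern.** The usual GEE sandwich variance is justified as the number of clusters grows. The number of patients per cluster does not help, because the variance of a clinic-level intervention effect is learned from the spread between clinics. With four clinics per arm that variance is biased low, and the statistic has far heavier tails than a normal variable.

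The article sees that eight clinics is a small number, but its remedies address other problems. Matching, risk scoring and propensity matching address baseline imbalance. Adjusting for the intracluster correlation addresses dependence between patients of one clinic. None repairs the variance estimate or the reference distribution. If GEE is run in its ordinary form, intervals for cost, utilization and patient experience will tend to be too narrow, and a chance difference between a few clinics could be read as an effect of the high-value elements.

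**Working it through.** The plan gives no type I error figure to reproduce. The check asks what ordinary GEE would deliver in this design.

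**Inputs from the article:** 8 clinics in 4 matched pairs, so k = 4 per arm; ICC 0.02; mean clinic size 10,000; hospitalization 14%.

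**Assumptions, not in the article:** two-sided alpha 0.05; uncorrected sandwich variance; normal critical value 1.96. The simulations of unequal clinic sizes also assume a clinic autocorrelation of 0.8, patient weighting, and a coefficient of variation (CV) of clinic size from 0 to 0.7.

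**1. Bias of the variance.** With equal clinics, the sandwich variance of an arm mean is the sum of squared residuals over k², that is s²(k−1)/k². The unbiased value is s²/k. The ratio is (k−1)/k = 3/4.

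**2. Unpaired, equal clinics.** The correctly scaled statistic follows t on 2k−2 = 6 df. The z test rejects when it exceeds 1.96 × √0.75 = 1.697. Type I error = 2·P(t₆ > 1.697) = **14.1%**.

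**3. Pair-based.** Four pair differences give the same ratio of 3/4, but 3 df. Type I error = 2·P(t₃ > 1.697) = **18.8%**.

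**4. Unequal clinic sizes, pairs ignored** (20,000 simulated difference-in-difference trials per row):

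| CV of clinic size | Type I error |
|---|---|
| 0 | 14.0% |
| 0.3 | 15.6% |
| 0.5 | 17.5% |
| 0.7 | 20.8% |

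A logistic GEE with equal clinics gave 15.3% in 300 runs. That is only a rough confirmation: its Monte Carlo margin is 1.96 × √(0.153 × 0.847/300), about 4 percentage points.

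**5. Pairs ignored, but matching effective.** If the clinics of a pair resemble each other in outcome change, the unpaired variance overstates the true one and offsets the bias. For equal clinics (400,000 runs; the article gives no such correlation):

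| Within-pair correlation | Uncorrected sandwich, z test |
|---|---|
| 0 | 14.1% |
| 0.2 | 10.9% |
| 0.3 | 9.1% |
| 0.5 | 5.9% |
| 0.7 | 3.1% |

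**6. Which corrections work.**

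| Analysis | Variance | Reference | Type I error |
|---|---|---|---|
| Unpaired | uncorrected | t, 6 df | 7.8% |
| Unpaired | Kauermann-Carroll type | z | 9.8% |
| Unpaired | Kauermann-Carroll type | t, 6 df | 5.0% |
| Unpaired | Mancl-DeRouen type | t, 6 df | 3.0% |
| Pair-based | bias-corrected | z | 14.5% |
| Pair-based | bias-corrected | t, 6 df | 9.2% |
| Pair-based | bias-corrected | t, 3 df | 5% at every within-pair correlation tried |

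The unpaired rows assume no within-pair correlation. With Kauermann-Carroll and t on 6 df, the rate falls to about 2.8% at correlation 0.3 and 1.7% at 0.5.

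**7. Permutation floor.** Four pairs allow 2⁴ = 16 allocations, so the smallest two-sided p is 2/16 = 0.125. Any p below 0.05 therefore rests on model assumptions.

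**The case against.** The strongest reply is that the article does not commit to a faulty test. Variance estimator, correction and degrees of freedom commonly belong in a SAP, which is not shown. GEE with a Kauermann-Carroll correction is still GEE and would contradict nothing in the text. The second stage is not defined and could be a clinic-level comparison with proper degrees of freedom.

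Much of this stands. A reader might infer that the trial's true type I error is 14–19%, or that false positives will be three times as frequent as stated. The documents support neither: they do not say that sandwich errors or a z test will be used, and they state no alpha to compare with. The rate also depends on the pairing; an analysis that ignores effective pairs can fall to 5.9% or 3.1%. Nor may one take clinic sizes of 3 to 20 providers as realised.

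The reply does not remove the point. The article discusses the small number of clusters, lists its remedies and goes as far as naming individual goodness-of-fit tests, yet every remedy listed is aimed elsewhere. The second stage is described as dealing with changes over time, which is not a test on clinic summaries. The method is fixed and, in its ordinary form, does not suit eight clusters.

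**Conclusion.** The concern holds in conditional form. GEE is the named method for eight clinics in four matched pairs, and nothing stated corrects its small-sample variance bias or its large-sample reference distribution.

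The size rests on three assumptions that the article neither makes nor excludes: uncorrected sandwich errors, a normal reference and a two-sided 5% level. Under these, type I error is about 14% (equal clinics, unpaired) to 19% (pair-based). Unequal clinics push the unpaired figure up, to about 21% at an assumed size CV of 0.7. Ignoring the pairs when matching is strong pulls it down, possibly below 5%. The direction of the error thus depends on choices that the text leaves open, which is the reason to settle them beforehand.

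**What to change.** Prespecify one of the following as the primary inference, before any primary-outcome analysis:

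- **Pairs respected:** obtain a risk-adjusted pre-post change for each of the eight clinics, take the four within-pair differences, and test their mean with t on 3 df; or
- **Pairs not modelled:** keep GEE with a bias-corrected sandwich of Kauermann-Carroll type and t on 6 df, stating that this is conservative when matching is effective.

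The degrees of freedom must follow the pairing: a pair-based variance referred to t on 6 df still gives 9.2%. Adjust for risk at patient level and enter no further clinic-level covariates, because only 3 or 6 df exist. State alpha and sidedness. If a permutation result is reported, it should respect the pairs and give its floor of 0.125; it cannot confirm a finding at 5%.

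The work is wording and a software option. The cost is precision. With equal clinics and the same point estimate, the half-width relative to an uncorrected z interval rises by 2.447/1.697 = 1.44 (t on 6 df, pairs ignored) or 3.182/1.697 = 1.88 (t on 3 df, pair-based), each against the uncorrected interval of the same analysis. The section on ethical approval and trial status reports that primary-outcome analysis had not begun at submission, so at that point the change could still be made in advance.
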